## 3.8 Study procedure

The study coordinator and the research assistants will complete a baseline assessment for the illegible participants. This will involve a survey to collect sociodemographic variables, measuring BP, anthropometric measurements (Height, weight and waist circumference) and lifestyle behaviour. Patients with uncontrolled blood pressure will be randomized either control arm (usual care) or intervention arm (Figure 1). The intervention will include a multicomponent community health worker–led home intervention (health coaching, home BP monitoring, BP audit and feedback, physical activity program to be implemented over a period of six (6) months. Participants randomized to the intervention will receives 2 home visits by the trained CHW over a period of 1 month, followed by monthly follow-up visits for a period of 6 months. The initial visit will involve a 90-minute home visit to discuss general knowledge about hypertension and offer tailored counselling on lifestyle modification as well as set physical activity targets. Subsequent monthly visit will be focused on social support, goal setting, problem solving, and maintaining motivation to meet set targets. The visits will involve BP monitoring during which the client and CHW will evaluate the BP and physical activity targets.

To assess the outcome of the intervention the survey conducted at baseline will be conducted by two trained research assistants (who were not part of and have no relationship with the CHWs team) to evaluate the participants at 1) 3 months and 2) 6 months when the intervention has ended. The research assistants will be blinded to the randomization status of the participants. The home visits/clinic visit for evaluation will be scheduled during the first half of the day to minimize the effect of diurnal variations in BP.

Materials to be used will include automatic BP machine, tape measure, a bathroom weighing scale, smart watch fitness monitor and a smart phone with intervention protocol detailing the health education on lifestyle intervention for reducing BP. A paper-based protocol will also be provided for back-up.

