## 3.4 Sample size and power calculation

With changes in BP as the primary outcome we calculated a sample of 52 between the 2 groups to show changes in BP between the intervention and control groups at a significance level of 0.05 for a two-sided test with 80% statistical power of finding a large effect (*Cohen’s d*=0.80). This study will be underpowered to find significantly small effect (*Cohen’s d*=0.30) and moderate effect (*Cohen’s d*=0.50), however, we will be able to calculate an effect size and the direction of its impact.

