## 3.5 Sampling and participants recruitment

We will randomly sample 2 wards in Ruiru and Juja Sub-counties. All participants in the selected wards with uncontrolled BP willing to participate will be recruited into the study. Screening will be done at the community level. CHW will conduct door to door screening for hypertension using digital BP machines for all adults in the selected wards. The CHW will document the BP readings and anthropometric measurement in a paper form register. The CHW will offer a referral letter (to the nearest level 3 hospital) for all participants with uncontrolled BP. The CHW will furnish the study coordinator with the particulars of such participants for follow-up and possible recruitment into the study. Participants will receive a refund of the transport cost upon presenting the referral note so as to encourage them to turn up at the health facility. Participants who do not show up in the facility within 48 hours of screening will be traced through home visits. The participants will be recruited for the RCT at the level 3 health facility in the respective wards after reassessment by the clinician and commencement of medical management.

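### Recruitment and the start of medical management run through ward facilities, but ward is named neither in the randomisation nor in the BP model: a modest, avoidable loss of precision with 52 patients

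*Protocol*

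**What the plan says.** Protocol section 3.5 sets the site structure: "We will randomly sample 2 wards in Ruiru and Juja Sub-counties". Patients with uncontrolled BP found at community screening are referred to a level 3 facility and are then "recruited for the RCT at the level 3 health facility in the respective wards after reassessment by the clinician and commencement of medical management".

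Section 3.8 describes allocation: "Patients with uncontrolled blood pressure will be randomized either control arm (usual care) or intervention arm". Neither this section, nor section 3.1, nor the abstract gives a sequence method, block structure, ratio or stratification factor.

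Section 3.9 adjusts the BP model (GEE) for intervention group, baseline characteristics (not itemised), healthy diet and demographics. Section 3.6 gives age, sex and occupation as the demographics. Ward, facility and sub-county are named in none of these places.

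The primary outcomes in section 3.6 are the arm differences in systolic and diastolic BP change from baseline to end line. On size, section 3.4 states: "we calculated a sample of 52 between the 2 groups to show changes in BP between the intervention and control groups", with "80% statistical power of finding a large effect", defined as Cohen's d = 0.80.

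**The concern.** Medical management begins around trial entry, at the facility in the patient's ward, and can move BP in both arms. If facilities differ in how much BP falls under usual care, ward predicts the primary outcome. A strong, known predictor of outcome is normally balanced by design and fitted in the model. Otherwise a chance excess of one ward in one arm shifts that trial's estimate, and the variation between wards stays in the residual error.

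These are two views of one loss of precision and should not be added together. It matters somewhat more here than in a larger trial. The sample is sized for a large effect only, the protocol concedes low power below that, and a main product is an effect size to inform a later full trial.

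**Working it through.** **Inputs from the protocol.** N = 52, two-sided alpha 0.05, power 80%, d = 0.80 (section 3.4); two wards (section 3.5).

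**Assumptions.** The protocol gives no allocation ratio, ward sizes, SD in mmHg or ward difference. I assume 26:26 arms, 26 patients per ward, a total SD of BP change of 12 to 18 mmHg, and a ward gap *w* of 4 to 10 mmHg. A linear model of BP change stands in for the GEE.

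**1. The protocol's own figure.** A two-sample t-test at d = 0.80 needs 25.52 per arm, rounded up to 26, so 52 in total. This agrees with section 3.4. Power at 26 per arm is 80.7%.

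**2. Chance imbalance by ward.** Let X be the number of ward-A patients in the intervention arm. X is hypergeometric (26 drawn from 52, of whom 26 are from ward A). The difference in ward share is (2X − 26)/26, with SD 0.14.
- At least 20 points requires |X − 13| ≥ 3: probability 0.165.
- At least 30 points requires |X − 13| ≥ 4: probability 0.051.

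**3. Shift in the estimate.** Shift = imbalance × *w*. At 20 points this is 0.20 × 4 = 0.8 mmHg to 0.20 × 10 = 2.0 mmHg. The standard error of the arm difference is SD × √(2/26): 12 × 0.277 = 3.3 mmHg and 18 × 0.277 = 5.0 mmHg.

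**4. Standard error saved by fitting ward, with ward balanced across arms.** Saving = 1 − √(1 − (w/2)²/SD²).

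| Ward gap | SD 12 | SD 18 |
|---|---|---|
| 4 mmHg | 1.4% | 0.6% |
| 6 mmHg | 3.2% | 1.4% |
| 10 mmHg | 9.1% | 3.9% |

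**5. Power.** Let *g* be the ward gap in within-ward SDs and take d = 0.80 on that scale. Omitting ward multiplies the standard error by √(1 + g²/4), so the usable effect is 0.80/√(1 + g²/4).

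| g | SE ratio | Power without ward |
|---|---|---|
| 0 | 1.000 | 80.7% |
| 0.2 | 1.005 | 80.4% |
| 0.5 | 1.031 | 78.4% |
| 0.8 | 1.077 | 74.7% |
| 1.0 | 1.118 | 71.6% |

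On this scale g = w/√(SD² − w²/4). The mmHg ranges above therefore run from g = 4/√(324 − 4) = 0.22 to g = 10/√(144 − 25) = 0.92, so g = 1.0 lies slightly beyond them.

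**6. Simulation (20,000 trials per scenario).**
- Unstratified, no ward term: mean estimate 0.80 for a true 0.80; type I error 5.2% (g = 0.5) and 5.0% (g = 1.0).
- Unstratified, ward fitted: power 79.8% and 80.4%.
- Stratified, ward fitted: power 80.6% and 80.9%.
- Stratified, ward not fitted: type I error 4.6% and 3.0%, which is conservative.

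Most of the gain comes from the ward term. Stratification adds balance and a little more.

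**The case against.** The protocol is silent on how patients are allocated, and silence is not a statement that allocation is unrestricted. Section 3.8 also points to a figure that is not reproduced in the text available. The baseline characteristics in section 3.9 are left open, so a later analysis plan could include ward, and the exact covariate list is often settled there. The trial is for feasibility and preliminary efficacy and states its limits: "This study will be underpowered to find significantly small effect". Up to a ward gap of 0.5 SD the loss is about two power points, and the gap itself is assumed.

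Most of this stands, and it fixes the severity at minor. What it does not answer is timing: a ward term can be added in an analysis plan, but stratification cannot be added once patients have been allocated. It belongs in the protocol.

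A reader might infer more than the documents support:
- **Confounding or a false-positive risk.** Randomisation makes ward imbalance a chance event, and the ordinary standard error already contains the ward variation. The simulation shows no bias and type I error at about 5%.
- **Imbalance as the usual case.** A 20-point difference in ward share arises in roughly one allocation in six.
- **Separate CHWs for each ward, acting as a background factor.** Section 3.5 says only that "CHW will conduct door to door screening for hypertension using digital BP machines for all adults in the selected wards". It does not say that CHWs are separate by ward, and section 3.8 gives the CHW home visits to the intervention arm only. The point rests on the facility and the management begun there.

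**Conclusion.** The point holds as a modest, avoidable loss of precision. The structure in section 3.5 makes ward, or recruiting facility, a plausible predictor of BP change, and neither the allocation nor the named BP covariates use it.

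The size depends on a ward gap that the protocol does not give. It is negligible at 4 mmHg (standard error saving of 0.6 to 1.4%) and noticeable only when the gap approaches one SD, where power falls by about nine points. Even a 20-point imbalance shifts the estimate by less than its standard error throughout the assumed range.

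The figures also rest on two equal wards and equal arms. Section 3.5 can be read as two wards per sub-county; four wards would change the numbers somewhat but not the conclusion. This is a cheap improvement of minor severity and does not invalidate the design.

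**What to change.** In section 3.8, state that randomisation is carried out separately within each ward (recruiting facility), in permuted blocks. In section 3.9, add ward as a fixed term in the BP models.

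Make both changes together, because stratifying without the term leaves the test conservative. With two or four wards, use a fixed effect; standard errors clustered on ward would be unreliable with so few.

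The cost is one allocation list per ward, one line in section 3.9, and one degree of freedom with two wards or three with four. The stratification must be in place before the first patient is allocated.

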# METHODOLOGY

3.1 Research design

This will be a randomized controlled trial (RCT). Hypertensive patient will be randomised to either CHW led lifestyle intervention or usual care arm. The intervention will be implemented for 6 months with outcome assessment at 3 and 6 months.

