## 3.7 Data for feasibility and acceptability assessment

At the end of the study, participants in the intervention arm will complete the Client Satisfaction Questionnaire(Larsen et al., 1979) to assess acceptability of the CHW intervention. In addition, 10 patients (purposively sampled to include both gender and different age groups) and CHWs from the intervention group will be targeted for in-depth interviews (IDIs) to understand their experiences and perceptions on the utility of the intervention in the control of hypertension. The IDI guide will cover questions on experiences from using the intervention and determinants of its use. We will assess feasibility of the intervention by examining recruitment rates, follow-up home visits completion rate, dropouts, and adherence to the individualized physical activity program.

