## 3.9 Data analysis

We will use STATA version 15 software for statistical analyses. The differences between the control and intervention groups on baseline demographics, biological and behavioral measures will be assessed using nonparametric (chi square test) and parametric tests(t-test) as appropriate. Generalized estimating equations (GEE) approach of Zegar and Liang(Zeger & Liang, 1986) will be used to analyze how BP vary over the six months after adjusting for intervention group, baseline characteristics and healthy diet while adjusting for demographic characteristics. For the secondary outcome variables, we will use GEE analysis for changes in BMI and mixed model analysis of changes in WHtR after adjusting for the interventions ,baseline characteritics and use of antihypertensives. The GEE model will be used to examine the association between the CHW intervention with BP control and normal BMI, reporting odds ratios, after controlling for baseline measurements and use of antihypertensive medication. Statistical significance will be considered at P < 0.05.

##

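### The 80% power in 3.4 holds only if there is no clustering by community health worker in the intervention arm; the protocol gives neither the number of workers nor their caseload, and the GEE described in 3.9 has no worker term

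*Protocol*

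**What the plan says.** Section 3.1 randomises individuals: "Hypertensive patient will be randomised to either CHW led lifestyle intervention or usual care arm". Under section 3.8 the intervention consists of CHW home visits: "Participants randomized to the intervention will receives 2 home visits by the trained CHW" in the first month, then monthly visits of coaching and target review. The usual care arm gets no such visits. Section 3.7 shows that more than one CHW delivers the intervention ("CHWs from the intervention group will be targeted for in-depth interviews"). Neither section gives the number of CHWs or the patients per CHW.

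Section 3.4 says "we calculated a sample of 52 between the 2 groups to show changes in BP between the intervention and control groups". Alpha is 0.05, two-sided, and the claim made for this sample is "80% statistical power of finding a large effect", taken as d = 0.80. It mentions no ICC, caseload or design effect. Section 3.9 uses a GEE to "analyze how BP vary over the six months after adjusting for intervention group, baseline characteristics and healthy diet", together with demographic characteristics. CHW is not among the listed terms, and the clustering unit is not named.

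**The concern.** The CHW's counselling and motivation are the treatment, so results plausibly depend on who delivers it. If several patients share a CHW, their blood pressure changes may be correlated, and only in the intervention arm. The GEE as described deals with blood pressure over time within a patient. If nothing is added for CHW, the variance between CHWs is missing from the standard error of the arm comparison. The interval is then too narrow, the false-positive rate exceeds 5%, and one unusually good or poor CHW can be read as an effect of the programme.

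The trial is also meant to inform a future fully powered RCT. Its planners would need an honest interval and some idea of variation between CHWs. That variation cannot be recovered later if CHW identity was never recorded.

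**Working it through.** **Inputs from the protocol.** Total 52, two-sided alpha 0.05, power 80%, d = 0.80 (all 3.4); individual randomisation (3.1); CHW delivery in one arm (3.8); at least two CHWs (3.7).

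**Assumptions, because the protocol gives no figure.** 1:1 allocation, so 26 per arm; no dropout; equal caseloads m = 26/K for K CHWs; ICC of 0.02 to 0.10 for blood pressure change.

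**Step 1: reproduce the stated figure.** For a two-sample t-test with independent patients and SD = 1, the standard error is √(2/26) = 0.277 and the noncentrality is 0.80/0.277 = 2.88. With 50 degrees of freedom, power is 80.7%. With 25 per arm it is 79.1%. So 26 per arm, or 52 in total, is exactly the independent-patient answer, with no allowance for clustering.

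**Step 2: add clustering in one arm.** The design effect in the intervention arm is DE = 1 + (26/K − 1) × ICC. The variance of the contrast is (1 + DE)/26 instead of 2/26, so the true standard error is √((1 + DE)/2) times the naive one.

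For K = 3 and ICC 0.05:
- DE = 1 + (8.67 − 1) × 0.05 = 1.38.
- The standard error ratio is √(2.38/2) = 1.09.
- Naive type I error ≈ 2[1 − Φ(1.96/1.09)] ≈ 7.2%.
- For a test with the correct standard error, noncentrality is 0.80/√(2.38/26) = 2.64 and power is 73.6%.

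The same steps for other values:

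| CHWs (K) | ICC | DE | Naive type I error | Power, corrected test |
|---|---|---|---|---|
| 2 | 0.10 | 2.20 | about 12% | 61% |
| 3 | 0.05 | 1.38 | about 7% | 74% |
| 3 | 0.10 | 1.77 | 9-10% | 67% |
| 6 | 0.02 | 1.07 | 5.4% | 79.5% |
| 6 | 0.05 | 1.17 | about 6% | 78% |
| 10 | 0.05 | 1.08 | about 5.5% | 79.2% |
| 13 | 0.05 | 1.05 | about 5.3% | 79.8% |
| 26 | any | 1.00 | 5.0% | 80.7% |

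Simulation of 40,000 unadjusted t-tests per cell agrees with the type I errors to within about 0.2 percentage points.

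**Step 3: keep the two tests apart.** The last two columns describe different tests. The type I error is for the unadjusted test; the power is for a test with a corrected standard error. At d = 0.80 the unadjusted test still rejects about 77-80% of the time across 3 to 6 CHWs. Its fault is an inflated error rate under the null, not a visible loss of rejections.

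**Step 4: few CHWs.** The corrected power above keeps 50 degrees of freedom. With Satterthwaite degrees of freedom reflecting the number of CHWs, power at ICC 0.05 is 67.2% (4 CHWs), 71.2% (5 CHWs) and 77.7% (10 CHWs).

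**The case against.** A reader might infer that participants share only a handful of CHWs, and that the standard errors are therefore certainly too small. The protocol does not support this. It never gives the number of CHWs, and door-to-door screening of all adults in the sampled wards (3.5) does not settle how many deliver the intervention. With one patient per CHW there is no effect, and with 10 or more at ICC 0.05 less than 2 points of power are lost. This objection stands, and the conclusion has to be conditional.

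A reader might also infer that section 3.9 has decided to ignore CHWs. It has not: it names no clustering unit or variance estimator, and a statistical analysis plan, not at hand, could supply both. So the analysis side is a matter left open rather than a demonstrated error. The power statement is different: section 3.4 gives a figure, and that figure assumes independence.

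It can also be said that the trial is preliminary and already admits low power for d = 0.30 and 0.50. That limits the consequence but does not remove it, because the protocol still claims 80% power, sets an effectiveness objective and applies a 0.05 significance threshold.

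Finally, a random effect cannot simply be inserted into a GEE, which is a marginal model. That is correct, and the fix below respects it.

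**Conclusion.** The point holds in conditional form. The figure of 52 is arithmetically right on its own inputs, but those inputs assume no CHW effect, and the protocol does not give the reader the means to judge whether that is reasonable. If CHWs carry several patients and the ICC is above zero, a standard error that ignores CHW is too small and a valid test has less than 80% power at d = 0.80.

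Over 3 to 6 CHWs and ICC 0.02 to 0.10, naive type I error runs from about 5.4% to 9-10%, and corrected-test power from 79.5% down to 67%. Two CHWs would be worse; ten or more at ICC 0.05 would make the matter negligible. All of this rests on the assumed number of CHWs and ICC, equal caseloads, 1:1 allocation and no dropout. The change is worth making because it is cheap and because CHW identity must be captured during the trial.

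**What to change.** 1. In 3.6 or 3.8, state the planned number of CHWs and their expected caseload, and record the CHW identity for each intervention participant.
2. In 3.4, say that power is 80% at d = 0.80 only if there is no CHW clustering, and give the range above.
3. In 3.9, keep the GEE as primary and add a sensitivity analysis of the primary blood pressure contrast: a mixed model with a CHW random effect in the intervention arm only, with small-sample degrees of freedom. If there are too few CHWs to estimate that variance, report instead the primary interval recomputed at fixed ICCs of 0.02, 0.05 and 0.10, multiplying the standard error by √((1 + DE)/2) with the caseloads observed.

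Simply clustering the GEE on CHW is not a safe substitute, since robust standard errors are themselves biased downward with few clusters.

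The cost is one data field, one secondary model, somewhat wider intervals in that analysis, and a poorly estimated CHW variance when CHWs are few. No extra enrolment is proposed.

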## 3.6 Data collection

An adapted WHO stepwise questionnaire will be used to collect information on demographic characteristics (age, sex, occupation), history of hypertension, other CVD risk factors, and health behaviours (smoking, alcohol drinking, diet, and physical activity) of participants at baseline and follow-up visits. The international physical activity questionnaire (IPAQ)(Craig et al., 2003) will be used to collect data on physical activity. The tools will be translated and validated in the local context. We will collect detailed data on patients care cascade during the home visits and monitor their ability to control their BP with the combination of medical management and the CHW intervention. Three BP measurements, body weight, height and waist circumference will be obtained at each data collection visit by outcome assessors masked to intervention assignment.

The primary outcomes will be the differences in systolic and diastolic BP changes from baseline to the end line survey. Secondary outcomes will include the proportion of patients with controlled hypertension (BP <140/90 mm Hg) ) according to the Kenyan national guidelines(Division of Non-Communicable Diseases-Ministry of Health, 2018), body composition – Body mass index(BMI), waist circumference . Low physical activity will be defined as less than 150 minutes of moderate physical activity or 75 minutes of vigorous activity each week. To assess the outcome of the intervention the survey conducted at baseline will be conducted at 3 months of follow-up and at the end of 6 months of intervention.

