|  | *The last question is about the time you spent sitting on weekdays during the last 7 days. Include time spent at work, at home, while doing course work and during leisure time. This may include time spent sitting at a desk, visiting friends, reading, or sitting or lying down to watch television*.  During the last 7 days, how much time did you spend sitting on a week day? | 1.…………… hours per day  2……………. minutes per day  Don’t know/Not sure |
| **History of Raised Blood Pressure** | | |
|  | Have you ever had your blood pressure measured? |  |
|  | Have you ever been told by a doctor or other health worker that you have raised blood pressure or hypertension? |  |
|  | Are you on any treatments/advice for high blood pressure? | |
|  | Drugs (medication) that you have taken in the past two weeks |  |
|  | Advice to reduce salt intake |  |
|  | Advice or treatment to stop smoking |  |
|  | Advice to start or do more exercise |  |
| **Step 2 Physical Measurements** | | |
|  | Interviewer ID |  |
|  | Device IDs for height and weight |  |
|  | Height(cm) |  |
|  | Weight(kg) |  |
|  | **For women:** Are you pregnant? |  |
|  | Waist circumference(cm) |  |

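### The assessors who must stay masked also ask about activity and lifestyle advice, on a form that prints these items before waist, and no step keeps participants from disclosing their arm

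*Protocol*

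**What the plan says.** **Masking.** Section 3.6 says that three BP measurements, weight, height and waist "will be obtained at each data collection visit by outcome assessors masked to intervention assignment". Section 3.8 repeats the claim: "The research assistants will be blinded to the randomization status of the participants".

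**The survey.** Section 3.6 says that "the survey conducted at baseline will be conducted at 3 months of follow-up and at the end of 6 months of intervention". Section 3.8 says that this repeat survey "will be conducted by two trained research assistants (who were not part of and have no relationship with the CHWs team").

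**The form.** Appendix 2 runs through demographics, tobacco, alcohol, diet, the IPAQ activity questions and the history of raised BP. The history section asks about medication and about advice on salt, smoking and exercise (the last item reads "Advice to start or do more exercise"). The final section, "Step 2 Physical Measurements", has fields for height, weight and waist circumference. It shows no BP field.

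**What the intervention arm receives.** Section 3.8 describes a 90-minute first home session on hypertension, lifestyle counselling and activity targets, then monthly CHW visits. The study materials listed there include a "smart watch fitness monitor and a smart phone with intervention protocol". Section 3.7 adds that, at the end of the study, "participants in the intervention arm will complete the Client Satisfaction Questionnaire".

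**The concern.** Participants and CHWs know the allocation, so assessor masking is the main protection of the measured outcomes against detection bias. The people to be masked are also the interviewers. The interview covers the topics on which the intervention arm has been coached each month, and a question about exercise or salt advice invites a participant to mention the CHW programme. If that happens before the tape measure comes out, the assistant measures waist knowing or guessing the arm.

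At stake is a difference between arms that comes from how measurements are taken and not from the intervention. Tape position is an operator's judgement. With BP, the assistant still controls rest and cuff placement. The protocol intends to report an effect size and its direction even where it is underpowered (Section 3.4), so a small bias would matter to that use.

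**Working it through.** The main check is a comparison of sections; arithmetic serves only for scale.

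**1. Who asks and who measures.** Section 3.6 requires masked assessors for BP and anthropometry. Section 3.8 assigns the repeat survey and the evaluation at 3 and 6 months to two assistants and calls them blinded. Interviewer and masked assessor are the same people.

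**2. Order of the visit.**

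| Source | Order given |
|---|---|
| Section 3.8, description of the baseline assessment | sociodemographic variables, BP, anthropometry, lifestyle behaviour |
| Appendix 2, printed form | demographics, behaviours including diet, IPAQ, treatment and advice, then height, weight and waist; BP not shown |

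Anthropometry comes before lifestyle behaviour in the text and after it on the form. Neither place is labelled a fixed visit sequence. For waist, the only printed form puts the advice items first. For BP, the form gives no position.

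**3. What the answers can reveal.** The items ask about advice in general and name neither the CHW nor the study arm. An answer can hint at the arm without stating it. The exposure lies in what an open-label participant adds in conversation.

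**4. Stated safeguards.** The assistants are independent of the CHW team. That closes the route from CHW to assessor and leaves the route from participant to assessor open. The protocol has no instruction to participants, no measure-first rule and no separation of survey staff from measurement staff.

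**5. Scale, on assumption only.** The documents give no figure for measurement bias and no standard deviation (SD) for BP.

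- The plan's own figure: d = 0.80, two-sided 0.05, 80% power. The exact two-sample t-test needs 25.52, so 26 per arm and 52 in total, with power 80.7% (1:1 allocation assumed). The stated 52 reproduces. The point does not depend on it; it only supplies n = 26 below.
- Suppose there is no true effect but a differential bias of b SD. For a simple t-test, the noncentrality is b × √(n/2) = b × √13 = 3.606b, with 2 × 26 − 2 = 50 degrees of freedom. The two-sided 5% error rate becomes:

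| Assumed b | Noncentrality | Error rate |
|---|---|---|
| 0.1 | 0.36 | 6.4% |
| 0.2 | 0.72 | 10.9% |
| 0.3 | 1.08 | 18.6% |

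- In mmHg, with an assumed SD of 15, a bias of 1 to 3 mmHg systolic is 1/15 = 0.07 to 3/15 = 0.20 SD. The upper end is 0.20/0.80 = one quarter of the planned effect.

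These figures show what such a bias would do. They are not evidence that it would occur.

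**The case against.** The strongest reply is that the primary outcome is better protected than the concern suggests. BP is read on an automatic machine, three measurements are set for every visit, and evaluations are scheduled for the first half of the day (Sections 3.6 and 3.8). This stands in good part: device and fixed number of readings leave less room for observer influence on BP than on waist. Rest and cuff placement remain with the assistant.

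A second reply is that the advice items do not separate the arms. Everyone is recruited after clinician reassessment and the start of medical management, and CHWs screened and referred patients in both arms (Section 3.5). Controls may therefore also report treatment or advice, or mention a CHW. This stands too. A reader might infer that the survey is bound to reveal the arm and that the blind must fail; the documents do not support that. What differs between arms is months of CHW coaching, which a participant may or may not mention.

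A third reply is that visit scripts belong in a procedures manual. That is fair for rest timing and wording. It does not cover the order, because the protocol prints a form and describes the assessment, and the two disagree.

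**Conclusion.** The point holds as an avoidable risk to the assessor blind, not as a demonstrated failure of it. The risk is clearest for waist, where the printed order puts the advice items first. It is possible for BP, whose place in the visit is not fixed. The size of any bias cannot be estimated from the documents, and the illustration above rests wholly on assumed values.

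Three stronger readings should be set aside:

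- A reader might infer that BP is taken after the survey. The form has no BP field, and Section 3.8 lists BP before lifestyle behaviour.
- A reader might infer that intervention participants arrive wearing a fitness watch. It appears once, in a general list of materials; who wears it, and whether it is present at assessment, is not stated.
- A reader might infer that the satisfaction questionnaire unmasks the assistants at 6 months. That requires the same assistants to give it at or before the 6-month measurements, which no section says. The timetable in Section 3.11 puts end-line collection in Month 9 and the qualitative acceptability work in Month 10; it does not place the questionnaire itself.

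Nor do the documents show that every error would favour the intervention. The change is still worth making because it is specific and cheap.

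**What to change.** Amend Section 3.8 and reorder Appendix 2 so that they agree:

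- At 3 and 6 months, take the three BP readings and the anthropometry first, after a seated rest. Add a BP field to the form at that place. Give the diet, activity, medication and advice items only afterwards.
- Before each evaluation, ask participants not to mention CHW visits and to put away any programme materials. State who wears the watch; if participants do, ask them to remove it for the visit.
- Have the satisfaction questionnaire completed after the participant's 6-month measurements, either by self-completion or with someone other than the masked assistants.
- Optionally, have the assistant record a guess of the arm straight after the measurements, so that the blind can be described in the report.

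The cost is one reordered form, a few lines in the visit script and, if wanted, one tick box. The downside is a few minutes of scheduled rest, since the interview no longer serves as the rest period. No extra staff are needed.
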